## Abstract

**Background:**

Diaphragm dysfunction is prevalent among individuals with asthma due to lung hyperinflation and hyperventilation in asthma paroxysm. This study was designed to evaluate the effect of the manual diaphragm release technique (MDRT) on diaphragm function in individuals with asthma.

**Methods:**

Adults with diagnosed stable asthma (n = 24), will be recruited from the General Hospital of Kifissia “Agioi Anargyroi” in Athens, Greece. The volunteers who meet the inclusion criteria will be randomly allocated to two groups: (a) the experimental group (n = 12) that will receive 12 sessions of MDRT in conjunction with breathing retraining exercises (BRE), and (b) the control group (n = 12) that will receive 12 sessions of BRE. Measurements will occur at three time points: before the initiation of treatment sessions (week 0), followed by 12 treatment sessions (week 6), and three months from the beginning of the trial (week 12). The main outcomes will be the diaphragm excursion (ultrasonography) and chest expansion (inch tape), with secondary outcomes the maximal respiratory pressures (digital pressure manometer), dysfunctional breathing (Nijmegen questionnaire), asthma control (ACT), dyspnea (Borg scale) and quality of life (SF-12v2).

**Discussion:**

The proposed protocol is the first to examine the effectiveness of MRDT on diaphragm’s function in individuals with asthma. Manual Therapy (MT) is a low-cost alternative and supplementary therapy to standard treatment procedures that might improve the biomechanics of respiration in pulmonary rehabilitation.

**Trial Registration:**

Registered on Clinical Trials.gov (ID: NCT05709054)

**Protocol version:**

29/09/2023

AbbreviationsACTAsthma Control TestBREBreathing Retraining ExercisesCOPDChronic Obstructive Pulmonary DiseaseCWEChest Wall ExpansionGOHKGeneral Oncology Hospital of KifissiaMDRTManual Diaphragm Release TechniqueMTManual TherapyNQNijmegen QuestionnairePRPulmonary RehabilitationRCTRandomized Controlled Clinical TrialUSUltrasonographyZOAZone Of Apposition

## Introduction

Due to its anatomical structure and contribution to minute ventilation (60–80%), the diaphragm is the most important respiratory muscle.
^
1
^
^–^
^
3
^ An impaired diaphragm is associated with respiratory symptoms such as dyspnea, intolerance to exercise and sleep problems.
^
4
^

Chronic obstructive pulmonary disease (COPD) and asthma are umbrella terms for various conditions characterized by chronic airway disease.
^
5
^ COPD and asthma patients frequently experience diaphragmatic dysfunction (DD).
^
6
^ The diaphragm’s ability to raise and expand the lower ribcage within the zone of apposition (ZOA), where the lower ribcage directly interacts with the diaphragm becomes compromised due to mechanical challenges. This is due to the diaphragm functioning at a disadvantageous shortened position caused by air trapping, which hinders its contraction capacity and increases the respiratory workload.
^
7
^

In COPD, air progressively remains trapped in the lungs due to airway constriction. The architecture of the thoracic cage is disrupted by this clinical condition during exercise and rest, reducing the diaphragm’s physiological advantage.
^
8
^
^,^
^
9
^ Similarly, Individuals with moderate to severe asthma may have pulmonary overstretching (asthma paroxysm), which can cause functional problems because it reduces expiratory flow (early airway closure), activates inspiratory muscles at the end of expiration, and reduces lung flexibility.
^
10
^
^–^
^
12
^ Although the underlying mechanisms for these two lung conditions, COPD and asthma, differ, both cause secondary complications (pulmonary hyperinflation, hyperventilation syndrome). These features lead to similar pathological changes that impair the diaphragm’s ability to elevate and expand the lower ribcage.
^
13
^ Consequently, during inspiration, the lower ribcage’s transverse diameter may decrease.
^
14
^ It’s also important to note that the mechanical disadvantage of the diaphragm in asthma can result in an increased workload for all inspiratory muscles, particularly during exercise, where dynamic hyperinflation may occur, leading to heightened dyspnea.
^
15
^
^,^
^
16
^

Over the past few decades, two research questions have emerged concerning how physiotherapy can enhance the mechanical efficiency of the thorax and the effectiveness of respiratory muscles during breathing in people with obstructive lung diseases. Researchers, from 1990
^
17
^ up to 2015,
^
18
^ have made several hypotheses and implemented physiotherapy interventions to find which procedure is more appropriate to improve the effectiveness of mechanical functioning of the thoracic cage in people with pulmonary diseases. Breathing retraining exercises (BRE) are a widely used, productive method,
^
19
^
^–^
^
21
^ simple, safe, accessible, with a high level of evidence-based efficacy.
^
22
^
^–^
^
24
^

Finally, although specific diaphragm MT techniques have not been documented yet, recent studies have reported evidence for their positive effect on pulmonary rehabilitation (PR).
^
25
^ In particular, the manual diaphragm release technique (MDRT) aims to directly stretch the muscle fibers of the diaphragm, as detailed in Rochas’ research.
^
18
^ The study showed an improvement in diaphragm’s mobility, maximum inspiratory pressure (MIP), and exercise capacity (EC) in people suffering from COPD.
^
18
^ We deem it pertinent to mention that previous studies have demonstrated that even a single MT session can have a positive effect on chest wall mechanics, dyspnea, and peripheral oxygen saturation (SpO2) in individuals with COPD.
^
26
^
^,^
^
27
^ Therefore, dyspnea, being one of the primary symptoms of asthma, can adversely affect both exercise capacity (EC) levels and overall quality of life (QoL).
^
28
^
^–^
^
31
^ According to a study
^
26
^ a single MT session of soft tissue and joint mobilization immediately improved dyspnea (Borg Scale 0-10, pre: 2.3 ± 0.8 vs 1.8 ± 0.5). The authors reported that the mechanism underlying this improvement could be the increase in respiratory muscle length and thoracic cage flexibility induced by MT, consequently reducing breathing effort and the development of dyspnea in individuals with COPD.
^
32
^ As for asthma, there is currently no data regarding the efficacy of diaphragm MT methods, except for the pilot study conducted by Macias and colleagues,
^
24
^ and the study by Elnaggar and colleagues,
^
33
^ which investigated the efficacy of MDRT in children.

Considering the growing clinical interest in asthma and the recent publications in the field, we believe that a randomized controlled trial (RCT) targeting intervention on the zone of apposition of the diaphragm using the MDRT in adults with asthma for outcomes assessment is warranted.

### Objective of the proposed trial

The primary objective of this study is to explore the impact of MDRT on the diaphragm’s function, particularly on the length-tension relationship and chest wall expansion (CWE) in people suffering from asthma. Secondary improvements are expected in the domain of dyspnea, asthma control and dysfunctional breathing. The MDRT in people with asthma may contribute to better disease management.

## Methods

### Study design

The present RCT will be a single centric, two arm parallel equivalence randomized controlled study conducted in accordance with the CONSORT statement. This RCT followed the SPIRIT (Standard Protocol Items: Recommendations for Interventional Trials) statement.
^
35
^ The completed SPIRIT checklist of the study is uploaded into an approved open repository (Reporting guidelines paragraph). The study’s flowchart is shown in
Figure 1.

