	**Practice diaphragmatic and nose breathing retraining**	- Half-lying supine position - Pillows behind the head & knees - one relaxed hand over the stomach and the other on the upper chest and clavicle	- *“Close your mouth and try to breathe easily, slowly and softly through your nose”* - *“Be careful not to inhale with “big” breaths, try during inhalation to raise only the stomach”* - *“Exhalation is passive through the nose and lets your stomach fall gently”*		1S x 5BC	
	**Slow breathing and controlled breath holding after exhalation**	- Half-lying supine position - Pillows behind head and knees - One relaxed hand over stomach and the other on upper chest and clavicle	- *“Close your mouth and try to breathe easily, slowly and softly through your nose”* - *“Relax your shoulder & chest”* - *“Try to slow down your breaths”* - *“Sometimes it helps to count in your mind while you are breathing, e.g. breathe in for a slow count of 2 and breathe out for a slow count of 3until feel empty your stomach”* - *“Keep empty your stomach for 3-5 seconds”*		1S x 10BC	
	**New breathing pattern in everyday life activities and various positions**	- Supine - Semi-sitting - Sitting	- *“Try to breathe in and out slowly and through the nose, even in the most challenging conditions”* - *“You will be able to recognize faulty breathing patterns, and you will be able to correct them”* - *“Try to use a calendar or a mobile phone reminder to implement a diaphragmatic slow nose breathing pattern and breathing exercises”*		3S x 5BC	
	**Breathing control in speech**	- Supine - Semi-sitting - Sitting	- *“You must budget airflow to control the number of words you say per breath and the tone and loudness of particular words in a sentence”* - *“Apply a slow, through the nose, diaphragmatic breathing pattern at speech (max 4-6 words spoken during slow exhalation, with breathing pauses, and slow inhalations)”* - *“Breathe out so that your lungs feel empty, and, before inhaling again”* - *“At yawning and at sighing close your mouth”* - *“Poor voice quality (hoarseness, roughness, or a strained/strident voice) results from inadequate or badly controlled airflow. Speech prosody: rhythm and intonation”*		3S x 5BC	

Control Group: This group will receive only BRE, as mentioned in the intervention group.

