### Sample size calculation

The sample size calculation was based on an alpha (α) level of 0.01, a power (β) of 0.85, and a large effect size, Cohen’s d, of 1.86 for a two-tailed independent t-test. This effect size was calculated based on the results reported by Rocha et al. (2015),
^
18
^ specifically from the mean (SD) values of the control and experimental groups following six manual therapy intervention sessions. Furthermore, the calculation accounted for an anticipated attrition rate of approximately 15%, foreseeing the potential for participant dropout or exclusion. This comprehensive approach to sample size calculation ensures the robustness and reliability of the study’s findings, enabling a precise detection of the large effect size with high statistical confidence. This resulted in a total sample size of 24 people (12 per group) considering a withdrawal rate of 15%.
^
75
^

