### Statistical analysis

The investigation will employ IBM SPSS software, specifically version 28, as the primary analytical tool for comprehensive data processing. Descriptive statistics will be employed to elucidate the distributional characteristics of the dataset. Subsequently, the Shapiro-Wilk test will be utilized to assess data normality for each dependent variable (including US, CWE, ACT, NQ, SF-12v2, and Borg scale) independently. Should normality assumptions be met, parametric tests, specifically the 2×3 ANOVA repeated measures, will be employed, accompanied by Bonferroni adjustment, to investigate the interaction between intervention (experimental and control groups) and time points (0, 6, and 12 weeks). Moreover, to evaluate the homogeneity of variance, Levene’s test will be conducted. The predetermined level of statistical significance is set at p<0.05.

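### The Methods label the trial an equivalence study, but its objective, sample size and analysis all test for a difference, and no equivalence margin is stated

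*Protocol article*

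**What the plan says.** The protocol article names the framework once, under Study design: "two arm parallel equivalence randomized controlled study conducted in accordance with the CONSORT statement". The other design elements read as follows.

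- **Objective of the proposed trial:** "The primary objective of this study is to explore the impact of MDRT on the diaphragm’s function". It goes on: "Secondary improvements are expected in the domain of dyspnea, asthma control and dysfunctional breathing".
- **Interventions:** the experimental arm receives MDRT plus BRE. Of the control arm it says: "This group will receive only BRE, as mentioned in the intervention group". MDRT is thus an addition to a common background.
- **Sample size calculation:** "The sample size calculation was based on an alpha (α) level of 0.01", with "a power (β) of 0.85" and an effect size "of 1.86 for a two-tailed independent t-test". The effect size comes from an earlier trial of the technique in COPD. The result is 24 participants, 12 per group, allowing for 15% withdrawal.
- **Statistical analysis:** a 2×3 repeated-measures ANOVA with Bonferroni adjustment, used "to investigate the interaction between intervention (experimental and control groups) and time points (0, 6, and 12 weeks", with significance at p<0.05.
- **Conclusions:** the trial is expected to supply evidence that MDRT affects diaphragm function.

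The article states no equivalence margin, no equivalence test and no confidence-interval rule for concluding equivalence.

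**The concern.** Equivalence is a formal framework. It reverses the hypotheses: the null is that the arms differ by at least a stated margin, and the trial succeeds by rejecting it. In a trial that tests for a difference, the null is no difference, and failing to reject it establishes nothing about similarity. The framework therefore decides how a non-significant result may be read.

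Here the label points one way and every operative element points the other. If the label stands when the results are written up, a p-value above 0.05 in 24 people could be presented as showing that adding MDRT to BRE makes no difference. The plan supplies no margin against which such a statement could be judged.

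This is not a detail left to a statistical analysis plan. The article itself fixes the framework, the basis of the sample size and the test, and they disagree. A later plan could add a margin, but it could not turn a calculation for detecting d = 1.86 into one for equivalence.

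**Working it through.** **1. Reproduce the stated sample size.** Inputs from Sample size calculation: d = 1.86, two-sided alpha 0.01, power 0.85, attrition 15%, equal arms, independent t-test.

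Power comes from the noncentral t distribution with 2n − 2 degrees of freedom and noncentrality d·√(n/2).

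- n = 9 per arm: noncentrality 1.86 × √4.5 = 3.95, critical t (16 df) 2.92, power 0.830.
- n = 10 per arm: noncentrality 1.86 × √5 = 4.16, critical t (18 df) 2.88, power 0.883.

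So 10 evaluable per arm are needed. Inflating, 10 / 0.85 = 11.8, rounded up to 12 per arm and 24 in total. This matches the article exactly. Every input belongs to a test for a difference, and none is an equivalence margin.

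**2. Set the elements side by side.**

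| Element | Framework it serves |
|---|---|
| Study design | Equivalence (label only) |
| Objective | Difference: impact, improvements expected |
| Sample size | Difference: two-tailed t-test to detect d = 1.86 |
| Analysis | Difference: interaction test at p<0.05 |
| Conclusions | Difference: evidence of an effect |
| Margin, equivalence test | None stated |

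**3. What a non-significant result would mean.** This assumes a t-test at one time point without baseline adjustment, at two-sided 0.05. The 95% half-width is t(0.975, 2n − 2)·√(2/n) in SD units.

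- 12 per arm: 2.074 × √(2/12) = 0.85 SD.
- 10 per arm: 2.101 × √(2/10) = 0.94 SD.

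With 12 (10) per arm, the chance of a non-significant result is 78% (82%) when the true effect is 0.5 SD, and 53% (61%) when it is 0.8 SD.

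**4. What an equivalence test would deliver at this size.** The article gives no margin, so the margins here are assumptions. Further assumptions: TOST with each one-sided test at 0.05, true difference zero, unadjusted comparison at one time point. Equivalence is concluded if the 90% interval lies wholly inside the margin. Its typical half-width is 1.717 × √(2/12) = 0.70 SD with 12 per arm and 1.734 × √(2/10) = 0.78 SD with 10.

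| Assumed margin | Power, 12 per arm | Power, 10 per arm |
|---|---|---|
| 0.5 SD | 0.2% | 0.1% |
| 0.8 SD | 22% | 12% |
| 1.0 SD | 53% | 39% |

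The smallest margin reaching 85% power is about 1.30 SD with 12 per arm and 1.43 SD with 10.

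**5. Sensitivity to the analysis.** If change from baseline is compared, its SD is √(2(1 − r)) times the raw SD, where r is the correlation between baseline and follow-up. The article does not give r. With 12 per arm and margins in raw SD, power for 0.8 SD and 1.0 SD is about:

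- r = 0.3: 7% and 29%.
- r = 0.5: 22% and 53%.
- r = 0.7: 58% and 84%.
- r = 0.8: 83% and 97%.

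For 0.5 SD it does not exceed about 20% over this range.

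**The case against.** The strongest reply is that this is one adjective in a list of design descriptors. The section states no hypothesis, margin or decision rule, and the prose has other slips, such as labelling power as β. The rest of the article makes the intention plain, and correcting the word changes neither the sample size nor the conduct of the trial. Much of this stands: a wording slip is the likeliest explanation. It does not make the label harmless, because the label names the framework under which a null result is interpreted.

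Several stronger readings are tempting, and the documents do not support them.

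- **That the investigators plan to report a null result as equivalence.** No section says so. The label only leaves room for it, and the same misreading also occurs in trials labelled superiority.
- **That an add-on comparison can have no equivalence question.** One can ask whether adding a component makes no material difference. The article simply does not pose that question.
- **That the trial could show equivalence only within margins too wide to matter.** The article gives no minimal important difference for excursion or chest expansion, and step 5 shows how far the power depends on an unstated correlation.

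One numerical coincidence also deserves mention. If 1.86 SD were read as a margin, TOST at one-sided 0.01 with 10 per arm would have about 87% power. The article does not present 1.86 that way: it is an effect to be detected with a two-tailed test, taken from an earlier trial's group means. The classification therefore rests on the stated inputs and test, not on the figure of 24 alone.

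**Conclusion.** The equivalence label is wrong as written. The objective, sample size, analysis and intended conclusion consistently test for a difference, and the stated 24 reproduces exactly on that basis. Superiority is an inference from these elements, since the article never uses the word.

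The consequence is one of interpretation. With no margin and no equivalence test, a non-significant result cannot support a claim of equivalence under the design described. Under the simple analysis in step 3, such a result would be the more likely outcome even if the true benefit were 0.5 or 0.8 SD. The equivalence power figures are illustrations that rest on assumed margins, a true difference of zero, one-sided alpha 0.05 and an unadjusted comparison at one time point. They would change with the baseline correlation if change scores are analysed.

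The point is worth correcting because the label governs how the primary result is read. It does not undermine the sample size or the planned test.

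**What to change.** In Study design, replace equivalence with superiority, in the sense of a test for a difference. Add that a non-significant result will not be interpreted as equivalence, and that the between-group difference will be reported with its 95% confidence interval. The sample size stays at 24, and randomization and measurements are untouched.

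If equivalence is truly intended, the sample size and analysis sections do not serve it. A justified margin, an equivalence test and a restated sample size basis would then be needed. On the assumptions of step 4 with 85% power and 15% attrition, n per arm = 2[(z₀.₉₅ + z₀.₉₂₅)/margin]² (normal approximation). A 0.5 SD margin needs 77 evaluable per arm (182 in total), 0.8 SD needs 30 (72 in total) and 1.0 SD needs 20 (48 in total).

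The SPIRIT checklist is only pointed to, not shown; align it if it repeats the label.

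The cost is one word and one or two sentences, plus a dated note to the ethics committee. The Protocol amendments section says no further modifications could be made, and the trial started in January 2023. The change should therefore be recorded as a correction of wording, before the outcome data are analysed.

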**Figure 1. f1:**
[figure not shown]
Design of the trial that the flowchart was prepared in accordance with the SPIRIT statement.

### Setting

The laboratory of Advanced Physiotherapy at the Physiotherapy Department of the University of West Attica (UNIWA) in Athens will be responsible for coordinating the trial. The recruitment of the patients will be conducted from the Pulmonology Department of the General Oncology Hospital of Kifissia “Agii Anargiri” (GOHK) in Athens (Greece). The hospital’s research committee approved the protocol (4479/09-03-22). Interventions and assessments will take place individually (home-based treatment) in Athens (Greece).

### Recruitment procedures

The participants will be recruited from the GOHK. All participants will be out-patients with diagnosed stable asthma, referred by the director, pulmonologist, of the Pulmonary Department of the GOHK. The same pulmonologist will perform lung function testing on all participants (well-maintained and regularly calibrated equipment), will diagnose asthma and perform the measure of chest expansion. A radiologist will perform the ultrasonography (US) and a statistician will process the required analysis. Two separate physical therapists will implement the DMRT and BRE. All participants will read and sign the consent form. The declaration of consent refers to personal data privacy and participation protection. They will subsequently be informed about a) the objectives, methods, and details of the study, (b) that it will be the volunteers’ decision whether to take part or not, (c) they will always have the right to withdraw from the research even after signing, (d) they can also refuse to answer questions they will not wish or remain in the survey and (e) that the patient’s decision to participate will not affect the provision of our research services.

### Randomization and blinding procedures

Following the initial assessment, eligible volunteers will be randomly assigned to two experimental groups if they meet the inclusion criteria by the secretariat of the Pulmonology Department of the GCHAA. The randomization will be carried out using sealed envelopes. Individuals will have their allocation concealed through the use of sealed envelopes that are sequentially numbered and opaque.
^
36
^ The envelopes will be opened only by the primary researcher, who is responsible for the research project and coordination of the study. The pulmonologist who will perform lung function testing on all participants (well-maintained and regularly calibrated equipment), diagnose asthma and perform the measure of chest expansion, the radiologist who will perform the ultrasonography (US), and the two separate physical therapists, who will implement the DMRT and BRE will be unaware of the group allocation.

